### Interim analyses {21b}

No interim analyses will be performed.

### Methods for additional analyses (e.g., subgroup analyses) {20b}

A priori defined exploratory analyses will be performed to evaluate the effects of fundoplication on symptoms of GERD, dysphagia, regurgitation, and chest and abdominal pain. For patients with PEH recurrence, the differences in symptoms of those with a fundoplication will be compared to those without a fundoplication as another exploratory endpoint. Our a priori hypothesis is that a recurrent hiatal hernia with a fundoplication in the mediastinum is more symptomatic for patients than recurrences without a fundoplication in the mediastinum. Differences between groups will be tested and described as standardized effects using chi-square test or Fisher’s exact test for binary variables and Student’s *t* test or Wilcoxon rank sum test for continuous variables with a 95% confidence interval and a *P* value of <0.05 denoting statistical significance.

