##### Intervention description {11a}

Key steps of the operation are standardized. Skin preparation, hair removal, perioperative antibiotic administration, and venous thromboembolism prophylaxis are performed per Surgical Care Improvement Project protocol guidelines. Laparoscopic access to the abdomen is obtained by the operating surgeon through either Hasson or optical trocar entry depending on his or her standard practice. Additional laparoscopic ports are placed at the operating surgeon’s discretion to permit liver retraction, working ports, and assistant port(s) for additional retraction. The hernia sac is completely excised from the mediastinum and may be resected from the gastroesophageal junction per the discretion of the surgeon. If necessary for exposure, the short gastric vessels may be divided. The mediastinal esophagus is mobilized to allow for at least 3–4 cm of intraabdominal esophagus. After the surgeon is satisfied with the length and mobility of intraabdominal esophagus, the diaphragmatic crura are reapproximated with permanent suture. If Collis gastroplasty or mesh is deemed necessary, the patient will be excluded from the trial. However, fundoplication may be performed based on surgeon preference and indications, which will be documented.

After crural closure, the patient is randomized to the appropriate treatment arm. Randomization occurs in a 1:1 ratio using a computer-generated random allocation sequence to receive either no anterior gastropexy (control arm) or anterior gastropexy (intervention arm). A study coordinator and/or a research fellow is responsible for the randomization process.

If a patient is randomized to anterior gastropexy (intervention arm), this is performed as the next step of the procedure. Two 2-0 permanent sutures are placed in the midbody of the anterior stomach to provide fixation to the left upper quadrant abdominal wall below the costal margin. Two small incisions are made in the left upper quadrant to allow a suture passer to grasp the remaining ends of the sutures and externalize them from the abdomen at separate fascial punctures. The operation proceeds to the next step per individual surgeon practice. At the time of abdominal desufflation, the sutures are tied which fixates the stomach to the abdominal wall in this position.

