Anterior gastropexy, along with several other technical steps, serve as branch points during operative decision-making which may affect outcomes of PEHR. These include, but are not limited to the following: minimally invasive versus open approaches, various crural closure techniques, addition or avoidance of fundoplication, mesh use versus no mesh use, and the use or avoidance of anterior gastropexy. We chose to exclude patients with mesh at the hiatus because there is evidence that it, at most, delays early recurrence of paraesophageal hernias [2, 25]. Our primary endpoint of PEH recurrence at 1 year ± 6 months is a short to medium-term follow-up period, and mesh placement would likely be a confounder if included. Patients not eligible for a minimally invasive repair were similarly excluded since there is evidence, albeit retrospective in nature, that open PEH repair has lower recurrence rates compared to laparoscopic approaches [24, 29]. On the other hand, there is no evidence to suggest that a fundoplication affects recurrence rates after paraesophageal hernia repair [30, 31]. Therefore, fundoplications were allowed in this protocol per surgeon discretion and are not expected to confound the primary endpoint. We will analyze this assumption at the conclusion of the study with a multivariate logistic regression model in patients with and without a fundoplication. We also hypothesize that a recurrent hiatal hernia with a fundoplication in the mediastinum is more symptomatic than recurrences without a fundoplication in the mediastinum. A priori exploratory outcome analyses will be performed to examine this hypothesis. Since there is no evidence to show that a fundoplication decreases recurrence rates, and it has the potential for increased symptoms of dysphagia, regurgitation, and chest pain after recurrence, it is currently not our standard practice to routinely perform a fundoplication during paraesophageal hernia repair. This study will elucidate these hypotheses and help power a larger study for a more formal evaluation. Patients who have undergone a prior paraesophageal hernia repair, cruroplasty, or anti-reflux procedure or have had esophageal or gastric resections in the past were excluded due to the inability to control for the variable anatomy at the hiatus which could confound resultant effects on recurrence rates and patient-reported symptoms. For similar reasons, if a Collis gastroplasty is needed for a shortened esophagus, these patients are not randomized. Our group rarely performs this procedure and if needed, the anatomic variation in this scenario would not be representative of the standard patient in this study population.

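### The exploratory comparison of symptoms with and without fundoplication uses unadjusted tests on a surgeon-chosen procedure, so it is open to confounding by indication and by surgeon

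*Protocol article*

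**What the plan says.** Section {20b} of the protocol article (Methods for additional analyses) plans two exploratory analyses of fundoplication.

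- **Whole population:** "exploratory analyses will be performed to evaluate the effects of fundoplication on symptoms of GERD, dysphagia, regurgitation", with chest and abdominal pain completing the list.
- **Patients with recurrence:** "the differences in symptoms of those with a fundoplication will be compared to those without a fundoplication as another exploratory endpoint".

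The method follows in one sentence: "Differences between groups will be tested and described as standardized effects using chi-square test" or Fisher's exact test for binary variables, and Student's t or Wilcoxon rank sum test for continuous ones, with 95% confidence intervals and P below 0.05 as the significance criterion. No covariate, baseline score or surgeon term is named.

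Fundoplication is not allocated by the trial. Section {11a} states that "fundoplication may be performed based on surgeon preference and indications, which will be documented", section {10} leaves it to the surgeon, and the Discussion says the group does not do it routinely.

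On the use of the results, the Discussion says: "This study will elucidate these hypotheses and help power a larger study for a more formal evaluation".

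**The concern.** The question is worded causally, but the exposure is selected. If surgeons wrap patients partly because of their reflux or swallowing symptoms, wrapped and unwrapped patients will differ before surgery in the same symptoms that are compared afterwards. Surgeons may also differ both in how often they wrap and in their patients' symptoms. A chi-square or t test on follow-up symptoms cannot separate these differences from a consequence of the wrap.

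Two things are at stake. A significant difference could be reported as an effect of fundoplication when it reflects who received one. And the standardized effect could be carried into the sample size of a later study. The data that would reduce the problem are already collected: Table 1 marks all five symptoms preoperatively, and surgeon, hernia type, BMI and sex are covariates of the primary model.

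**Working it through.** **Is another planned model meant for this question?** The article has three candidates.

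| Place | Model | Question it answers |
|---|---|---|
| Primary outcome, section {20a} | Binomial regression with fundoplication, hernia type, BMI, sex and surgeon | Recurrence by randomised arm |
| Secondary outcomes, section {20a} | Mixed models, groups fixed, surgeon random | Symptoms, in the part of the plan that covers the secondary endpoints |
| Discussion | Multivariate logistic model, with and without fundoplication | Whether fundoplication confounds recurrence |

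None is assigned to symptoms by fundoplication. The only method given for that is the set of two-group tests in section {20b}.

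**The plan's own figure.** No stated number is in dispute. The sample size reproduces: 0.24 versus 0.09, two-sided 5%, 80% power gives 95 per arm. 95 / 0.80 = 118.75, so 119 per arm and 238 in total, against 240 stated. It is used here only for two counts:

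- evaluable patients: 240 × 0.80 = 192, or 96 per arm;
- expected recurrences: 96 × 0.24 + 96 × 0.09 = 23.04 + 8.64 = 31.68, about 32. With all 240 followed it would be 120 × 0.24 + 120 × 0.09 = 39.6, about 40.

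**Illustration of the bias.** The documents do not give the share wrapped, the baseline imbalance or the correlation between baseline and follow-up. All three are assumptions:

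- share wrapped 20% to 50%, that is 38 versus 154 up to 96 versus 96;
- baseline imbalance d = 0.2 to 0.5 SD;
- correlation r = 0.3 to 0.5;
- no true effect of fundoplication.

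Formulas, in SD units of the follow-up score:

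- spurious difference = d × r;
- SE = √(1/n₁ + 1/n₀);
- z = d × r / SE;
- rejection rate = P(Z > 1.96 − z) + P(Z < −1.96 − z).

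SE for 38 versus 154 = √(1/38 + 1/154) = 0.181. SE for 96 versus 96 = √(2/96) = 0.144.

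| d | r | Spurious difference | Rejection, 20% wrapped | Rejection, 50% wrapped |
|---|---|---|---|---|
| 0.2 | 0.3 | 0.06 SD | 6% | 7% |
| 0.3 | 0.5 | 0.15 SD | 13% | 18% |
| 0.5 | 0.5 | 0.25 SD | 28% | 41% |

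The range is therefore about 6% to 41% per symptom, against a nominal 5%.

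**Check by simulation.** 4,000 runs per setting with 192 patients, 20% to 50% wrapped, d = 0.3 to 0.5 and r = 0.3 to 0.5 gave unadjusted rejection rates of about 8% to 40%. A linear model adjusted for the baseline score gave a mean difference of about 0 and rejection rates of about 4% to 6%. That holds where the measured baseline score is the confounder. It says nothing about unrecorded indications.

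**The case against.** The strongest reply is that these analyses are labelled exploratory, no conclusion about gastropexy rests on them, and the Discussion defers the formal answer to another study. That stands, and it limits the weight of the point. It does not remove it, because the article still words the target as effects, sets a significance threshold, and expects the results to help power that study.

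Second, section {20b} does not say whether the outcome is a follow-up score or a change from baseline, and a t test on change scores would use the baseline. That is fair. But a change score would not fully remove the confounding, and surgeon and indication would still be left out.

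Third, the sentence on tests comes directly after the recurrence-only hypothesis, so its reach could be read more narrowly. Even so, it is the only method in the section, and no other is given for the whole-population analysis.

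Fourth, an even split of wrapped and unwrapped patients fits poorly with a procedure that is not routine. This stands. 96 versus 96 is the count by randomised arm, and with 20% wrapped the upper figure falls from 41% to about 28%. With 10% wrapped (19 versus 173) it would be about 18%.

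A reader might infer three stronger things that the documents do not support:

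- **That the result is known to be confounded.** Neither the size nor the direction of a bias can be derived from them.
- **That the trial will settle the fundoplication hypotheses.** The text promises to elucidate them and points to a more formal evaluation later.
- **That the randomised arm influences the choice of wrap.** The order of the operative steps makes this possible, but the article does not say when the wrap is decided, and nothing suggests that it happens.

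**Conclusion.** The point holds in a limited form. The article states a method that does not suit its question: unadjusted two-group tests for a procedure chosen by preference and indication. This is a matter of what is written, not of detail left to an unseen analysis plan. The comparison is open to confounding by indication and by surgeon.

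The false-positive range of about 6% to 41% is an illustration and depends wholly on the assumed share wrapped, imbalance and correlation. It is not an estimate for this trial.

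The recurrence-only comparison has a further limit. It selects patients on an event after randomisation, which baseline adjustment does not fully repair, and about 32 patients cannot carry a full covariate model.

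The change is worth making because it is cheap, but nothing in the randomised comparisons depends on it.

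**What to change.** 1. **Whole-population analysis:** replace the unadjusted tests with a regression of each follow-up symptom score on fundoplication (linear or logistic, as the score requires). Adjust for that symptom's baseline score, randomised arm, surgeon, hernia type, BMI and sex. Report an association with a 95% CI, make no significance claim, and state that unrecorded indications and surgeon preference may still confound it.
2. **Recurrence-only comparison:** adjust for the baseline symptom score at most, or describe the two groups with confidence intervals only. State that patients are selected on a post-randomisation event.
3. **Discussion:** say that any effect size taken forward to a larger study is an observational estimate.

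The cost is slightly more analysis work and a more cautious conclusion. No new data are needed.

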### Outcomes {12}

#### Primary outcome

The primary outcome of interest is radiographic paraesophageal hernia recurrence at 1 year postoperatively in patients receiving anterior gastropexy compared to those receiving no anterior gastropexy. An upper gastrointestinal series (UGI) or computed tomography (CT) scan will be obtained at the 1-year follow-up visit as per standard of care at our institution. Imaging obtained within the CCF system and at other institutions at the 1-year time point will be eligible for review provided that these are uploaded into Epic. Imaging will be reviewed by outcome assessors who are blinded to the treatment group and a consensus among assessors is required. A height of 2 cm of stomach, fundoplication or other abdominal organ (excluding the esophagus) above the diaphragm will constitute a radiographic recurrence, as previously described by Oelschlager et al. [25]. Herniation < 2 cm will not be considered a recurrence for the purposes of this study. Additionally, the need for reoperation secondary to fundoplication disruption, dysfunction, or slippage at any time during the study period will be considered a recurrence. We hypothesize that recurrence rates at 1 year after surgery for patients who receive anterior gastropexy will be decreased by 15% or more compared to those receiving no anterior gastropexy.

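### The exploratory comparison of any fundoplication versus none among recurrences does not match the hypothesis about a fundoplication in the mediastinum

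*Protocol article*

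**What the plan says.** The protocol article, Methods for additional analyses {20b}, sets out this exploratory comparison: "For patients with PEH recurrence, the differences in symptoms of those with a fundoplication will be compared to those without a fundoplication". The next sentence gives the hypothesis, that "a recurrent hiatal hernia with a fundoplication in the mediastinum is more symptomatic for patients than recurrences without a fundoplication in the mediastinum". The Discussion repeats the hypothesis in the same positional terms and adds: "A priori exploratory outcome analyses will be performed to examine this hypothesis". No comparison by wrap position appears anywhere in the article.

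The Primary outcome section defines who counts as a recurrence, by two routes. The first is anatomical: "A height of 2 cm of stomach, fundoplication or other abdominal organ (excluding the esophagus) above the diaphragm will constitute a radiographic recurrence". The second is not: "the need for reoperation secondary to fundoplication disruption, dysfunction, or slippage at any time during the study period will be considered a recurrence".

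Fundoplication is not randomised. Under Intervention description {11a}, "fundoplication may be performed based on surgeon preference and indications, which will be documented". The Discussion says that "it is currently not our standard practice to routinely perform a fundoplication during paraesophageal hernia repair". The share of patients expected to have a wrap is not stated.

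**The concern.** The hypothesis sorts recurrences by the position of the wrap. The analysis sorts them by whether a wrap was ever made. The recurrence definition separates these two groupings in two ways.

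- A patient with a wrap can recur because stomach or another organ is 2 cm above the diaphragm while the wrap stays below it. Under the hypothesis this patient belongs with the recurrences that have no mediastinal wrap. Under the plan the patient joins the wrap group.
- A patient reoperated for wrap failure counts as a recurrence with no requirement for herniation on imaging. Only a patient with a wrap can enter this way, so the comparison group has no counterpart.

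The article says the study will shed light on these hypotheses and help to power a larger one. A contrast that is diluted or shifted by the grouping would be a poor basis for sizing that study, and a reader would take it as evidence about mediastinal wraps when it is not purely that.

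**Working it through.** **1. Types of recurrence, side by side**

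| Recurrence | Group under the hypothesis | Group under the planned comparison |
|---|---|---|
| No wrap made, herniation of 2 cm or more | No mediastinal wrap | No wrap (agrees) |
| Wrap made and lying above the diaphragm | Mediastinal wrap | Wrap (agrees) |
| Wrap made but below the diaphragm, other organ 2 cm or more above | No mediastinal wrap | Wrap (misplaced) |
| Wrap made, reoperation for wrap failure, no 2 cm herniation | Not a case of the kind described | Wrap (no counterpart possible) |

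The first two rows carry information about the hypothesis. The last two contaminate the wrap group.

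**2. The plan's own figure**

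The article gives no figure for this comparison, so I start from the sample size. Inputs from Sample size {14}: control rate 0.24, reduction of 15 points (so 0.09), two-sided alpha 0.05, power 80%, 20% loss.

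Per arm, with the mean rate 0.165:

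n = [1.96 × √(2 × 0.165 × 0.835) + 0.8416 × √(0.24 × 0.76 + 0.09 × 0.91)]² / 0.15² = 94.9, so 95.

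95 / 0.80 = 118.75, so 119 per arm, against 120 stated. Power with 96 per arm is 0.804. The stated figure is reproduced when the 15% is read as absolute.

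**3. Number of recurrences available**

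- With 20% lost: 96 × 0.24 + 96 × 0.09 = 23.04 + 8.64 = 31.7, about 32.
- With none lost: 120 × 0.24 + 120 × 0.09 = 28.8 + 10.8 = 39.6, about 40.

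**4. Size of the groups (wrap share is an assumption)**

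Detectable difference at 80% power = (1.96 + 0.8416) × √(1/n₁ + 1/n₂), in SD units, out of 32 recurrences.

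| Assumed wrap share | Wrap / no wrap | Detectable difference | One reoperation-only case as share of wrap group |
|---|---|---|---|
| 20% | 6 / 26 | 1.27 SD | 1/6 = 17% |
| 30% | 10 / 22 | 1.07 SD | 1/10 = 10% |
| 50% | 16 / 16 | 0.99 SD | 1/16 = 6% |

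**5. Effect of the mismatch on the contrast (all shares and shifts are assumptions)**

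Let m be the share of the wrap group with a mediastinal wrap, d the true mediastinal effect, r the reoperation-only share and s the symptom shift in those patients. The rest of the wrap group is taken to score like the no-wrap group. Then

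expected contrast = m × d + r × s.

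- Dilution only (r = 0, d = 0.5 SD): 0.5 × 0.5 = 0.25 SD at m = 0.5, and 0.7 × 0.5 = 0.35 SD at m = 0.7.
- No true effect (d = 0), reoperated patients still worse when scored (s = +1 SD): r = 0.1 to 0.3 gives +0.10 to +0.30 SD.
- No true effect, reoperated patients relieved when scored (s = −0.5 SD): r = 0.1 to 0.3 gives −0.05 to −0.15 SD.
- Both mechanisms (d = 0.5 SD, r = 0.3): from 0.5 × 0.5 − 0.3 × 0.5 = 0.10 SD to 0.7 × 0.5 + 0.3 × 1 = 0.65 SD.

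The sign of s depends on timing. Under Statistical methods, Secondary outcomes, symptoms are scored at baseline, 30 days and 1 year, and the numeric scales look back 7 days. A patient reoperated before the 1-year visit is scored there after the correction.

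**The case against.** **This is an exploratory analysis in a condensed article, and details belong in the analysis plan.** The exploratory label stands: neither the primary result nor the randomised secondary comparisons depend on this. The second half stands only in part. The article does not leave the grouping open. It names one, and that grouping differs from the hypothesis beside it, so an analysis plan that followed it would carry the mismatch over. Recurrence in {20b} could be meant as radiographic recurrence only, which would remove the reoperation problem. The text does not say so, and the misplaced wraps would remain.

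**A reader might infer that the comparison cannot test the hypothesis at all.** The documents do not support that. Every recurrence with a mediastinal wrap falls in the wrap group, and every recurrence without a wrap lacks one in the mediastinum. The comparison is a misclassified proxy, not an empty one.

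**A reader might also infer that the plan favours the hypothesis by construction**, because reoperated patients were presumably unwell. That confuses the reason for reoperation with the score that is analysed. Misplaced wraps pull the contrast towards the null, and reoperation may have relieved symptoms before the 1-year score.

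**The reoperation range of 0.01 to 7% in Background and rationale might seem to give the size of the enrichment.** It does not. It concerns revision for a recurrent hiatal hernia, whereas the cases at issue are reoperations for wrap failure without 2 cm of herniation.

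**Conclusion.** The point holds as a mismatch between a stated hypothesis and the comparison fixed to examine it. Recurrences with the wrap below the diaphragm are misplaced and dilute the contrast. Reoperation-only cases can enter the wrap group alone and can bias the contrast in either direction.

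The size cannot be derived from the article, which gives neither the wrap share nor the rate of such reoperations. Under the assumed shares and shifts, a true 0.5 SD effect could appear as anything from 0.10 to 0.65 SD, and a true zero as −0.15 to +0.30 SD. These shifts are small beside the 1.0 to 1.3 SD that about 32 recurrences could detect. The harm is therefore mainly a wrong interpretation and a wrong planning estimate for the larger study.

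This is a minor point that is worth correcting because the remedy is cheap. The primary result is unaffected.

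**What to change.** - Have the blinded assessors record, for each recurrence, whether the fundoplication lies above the diaphragm. They already review the images against a definition that names the fundoplication, but the article does not say that they note which structure has herniated.
- Restate the comparison as mediastinal wrap versus no mediastinal wrap among anatomically documented recurrences. Include recurrences documented before or at a reoperation, so that patients whose wrap was found in the chest and corrected before 1 year are not lost.
- For reoperated patients use symptom scores taken before the reoperation where available, and state their timing. With scores scheduled only at 30 days and 1 year, some patients may have just the 30-day score.
- Report recurrences that rest on reoperation alone separately.

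The cost is one extra recorded field, a wording change and smaller groups in an analysis that is already small. Adjusting for baseline symptoms, given that the wrap is the surgeon's choice, is a separate and optional refinement that does not cure the mismatch.
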